### Participant timeline

The study time scheme for enrollment, interventions, and assessments is presented in Table 1.

### Sample size

The sample size was estimated based on the calculations performed using the StatsDirect statistical software (V.3.1.4, StatsDirect, Chesire, UK). A total of 72 participants will be required to show a difference of 30 mg/dl (1.7 mmol//l) and an SD of 41 (which corresponds to the standard deviation of the paired differences being 82) and standard deviations for observations within treatment being 58 at the 90th minute of the study (the primary endpoint), with *α* = 0.05 and 80% power—assuming a 20% withdrawal rate. The correlation was set to 0 (conservative approach). We assume that glycemia differences between the study groups mentioned above are significant for metabolic control.

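### On its own inputs, 72 enrolled with 20% withdrawal gives about 78% power rather than the stated 80%; the gap is minor and one sentence corrects it

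*Protocol article*

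**What the plan says.** The Sample size section of the protocol article puts the whole calculation into one sentence: "A total of 72 participants will be required to show a difference of 30 mg/dl", with "the standard deviation of the paired differences being 82" and "standard deviations for observations within treatment being 58 at the 90th minute of the study", at "0.05 and 80% power" and "assuming a 20% withdrawal rate". It also gives an SD of 41, sets the correlation to zero and calls that choice conservative. The Statistical analysis section makes all tests two-tailed, and the Trial design section describes a crossover with 1:1 allocation to the two sequences.

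The article gives neither the number of completers that 80% power requires nor the formula used to allow for withdrawal.

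**The concern.** A reader takes the sentence to mean that, if one participant in five withdraws, those who remain still give 80% power. The number enrolled, the effect, the SD, alpha, power and withdrawal rate are all printed, so this can be checked without outside figures, and they do not quite fit together.

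The stakes are modest. Stated power and the withdrawal allowance are what readers use to judge a null result, and what the team uses to judge how many losses it can absorb. If 80% power fails before withdrawal reaches 20%, the text should give the rate at which it does.

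**Working it through.** **Inputs.** Difference 30 mg/dl, SD of paired differences 82, within-treatment SD 58, SD 41, correlation 0, alpha 0.05, power 80%, withdrawal 20%, 72 enrolled (all from Sample size); two-sided tests (Statistical analysis); two sequences, 1:1 (Trial design).

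**1. Do the SDs agree with each other?** At zero correlation the SD of the difference is 58 × √2 = 82.0, and 82 / 2 = 41 is the SD of the half-difference, as used when the two sequences of a crossover are compared. All three figures agree.

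**2. Completers needed for 80% power.**
- Normal approximation, paired: n = ((1.9600 + 0.8416) × 82 / 30)² = 7.6577² = 58.64, so 59.
- Normal approximation, half-differences compared between sequences: n per sequence = 2 × 2.8016² × 41² / 30² = 29.32, so 30 per sequence and 60 in total. This is the same calculation, rounded up within each sequence.
- Paired t-test (non-central t): 60 completers give 79.6% and 61 give 80.3%, so 61. Using n − 2 instead of n − 1 degrees of freedom also gives 61.

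**3. Enrolment needed if 20% withdraw.** To keep n completers, enrol n / (1 − 0.2).

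| Method | Completers | Divided by 0.8 | Multiplied by 1.2 |
|---|---|---|---|
| Normal, paired | 59 | 73.75, so 74 | 70.8, so 71 |
| Normal, 30 per sequence | 60 | 75 | 72 |
| Paired t | 61 | 76.25, so 77 | 73.2, so 74 |

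Division by 0.8 gives 72 in no row. The stated figure appears exactly once, as 60 × 1.2, and the base of 60 follows from the article's own SD of 41.

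**4. Power that 72 delivers after 20% withdrawal.** 72 × 0.8 = 57.6, so 57 or 58 completers. The normal approximation is Φ(30√n / 82 − 1.96).

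| Completers | Normal approximation | Paired t |
|---|---|---|
| 57 | Φ(2.762 − 1.960) = 78.9% | 77.5% |
| 58 | Φ(2.786 − 1.960) = 79.6% | 78.2% |
| 72 (no withdrawal) | 87.4% | 86.5% |

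After 20% withdrawal the shortfall runs from 80 − 79.6 = 0.4 points to 80 − 77.5 = 2.5 points.

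**5. Withdrawal that 72 can absorb.** By paired t, 1 − 61/72 = 15.3%. With 60 or 59 completers as the requirement, 1 − 60/72 = 16.7% or 1 − 59/72 = 18.1%.

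**6. Sensitivity to the correlation.** The article gives no value other than zero, so the non-zero values below are assumptions. SD of differences = 58 × √(2(1 − ρ)); power by paired t.

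| ρ | SD of differences | Power, 57 completers | Power, 58 completers |
|---|---|---|---|
| 0 (article, SD rounded to 82) | 82 | 77.5% | 78.2% |
| 0.05 | 79.9 | 79.5% | 80.2% |
| 0.1 | 77.8 | 81.6% | 82.3% |
| 0.3 | 68.6 | 90.0% | 90.5% |

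**The case against.** The strongest objection is that the difference is close to rounding. By normal approximation with 58 completers, power is 79.6%, which anyone would report as 80%. The article does not say which routine its software used, so the largest gap (77 against 72) belongs to one method only; the smallest is 74 against 72. Zero correlation is openly a cautious choice: the same child eats the same meal on both test days, and a correlation of only about 0.05 would restore 80% with 58 completers. The 20% is an allowance, in a study of three consecutive days that recruits during hospitalization, and if everyone completes, power is 86% to 87%.

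Most of this stands, and it is why the point is minor. It does not make the sentence correct. The article chose zero correlation as its basis, and on that basis every method falls below 80% after the full 20% loss. The cushion from a positive correlation also depends on an analysis that uses the pairing. The Statistical analysis section names Student's t-test, the Mann-Whitney test and a baseline-adjusted linear regression without saying that they are within-child; a fuller plan may settle this, but the article does not.

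Two stronger readings are tempting. A reader might infer that the authors multiplied by 1.2 where they should have divided by 0.8. The match with 60 × 1.2 is exact, but neither 60 nor 1.2 is printed, so the mechanism remains an inference. A reader might also infer that the trial is underpowered and must enrol five more. The documents do not support that: five is the top of a range of 2 to 5, and the power lost is at most 2.5 points under an assumption that the article itself calls conservative.

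**Conclusion.** The point holds as a minor correction. With a difference of 30 mg/dl, an SD of paired differences of 82, zero correlation and two-sided alpha 0.05, 72 enrolled and 20% withdrawal give about 78% power by paired t-test and about 79% to 80% by normal approximation. The direction does not depend on the method; the size does. The result rests on the article's own inputs, on withdrawal reaching the full 20%, and on withdrawn children contributing nothing to the 90-minute comparison. The shortfall would be smaller or absent if fewer withdrew, or if a positive within-child correlation were exploited in the analysis. The design, the endpoint and the enrolment target are not called into question.

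**What to change.** Restate the sentence and leave enrolment at 72. For example: 72 enrolled, about 57 to 58 completers after 20% withdrawal, give about 78% power (paired t-test, SD of differences 82, correlation 0); 80% power needs 61 completers, that is, withdrawal of at most about 15%. If the authors prefer the normal approximation, they should name it and give its own figures: 59 completers, or 60 at 30 per sequence. In either case, state the number of completers required and how withdrawal was allowed for.

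The cost is one sentence and a slightly less favourable power figure. No participant is added and no analysis changes.

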### Randomization

The participants will be randomly assigned to two groups: SuBo-NoBo or NoBo-SuBo. The randomization list will be generated using the statistical program Stats Direct (V.3.1.4, StatsDirect, Chesire, UK). Blocked randomization (blocks of four) will be used to ensure a good balance of participant characteristics in each group. The randomization list will be kept by a staff member who is not involved in the trial.

### Blinding

All participants and investigators will be blinded to the study procedures. The investigator will be given randomly generated treatment allocations within sealed opaque envelopes. Once a patient has consented to enter the trial, an envelope will be opened, and the allocated treatment regimen will be applied. A nurse not involved in the trial will program the bolus of prandial insulin in compliance with the patient’s allocation found in the sealed envelope and calculated dose of insulin. The screen of the insulin pump will be covered by a piece of black tape to avoid interference. After completing the randomized controlled trial by all subjects, sealed envelopes containing the allocation group of each person will be handed to the principal investigator. The investigator will maintain blindness as much as possible. In cases of exceptional circumstances (e.g., when knowledge of the actual intervention is essential for further management of the patient), the intervention will be unblinded. The principal investigator, in cooperation with research physicians, will decide whether the unblinding procedure is necessary. The reason for unblinding will be reported in the patient’s CRF.

### Data collection and management

A CRF based on the International Conference on Harmonization Guidelines for Good Clinical Practice will be completed on paper for each participant. Data will be transferred to an electronic password-protected database.

The data will be double-entered with automatic checking for mismatches and out-of-range values. All study data documents will be stored in a locker within the study site available only to the staff involved in the research. Data concerning insulin requirements, HbA1c values, and anthropometric parameters will be gathered from non-compliant participants and those who cancel their consent. Only the involved researchers will have access to the dataset and the participant’s personal information. The data will not be shared with any company or founding institutions. They will also not influence the reliable presentation of the results. A draft of the final article with the outcomes will be revised by professional editing services in English. No later than 2 years after the data collection, we will deliver a completely deidentified dataset to an appropriate data archive for sharing purposes.

### Compliance

We will provide written feedback to all the parents and participants about the results of the study when the recruitment process is completed. During the study procedure, a research physician will visit the participant every 30 min (until 180 min), check the blood glucose level, and give a reminder on the rules of the study (i.e., no snacking, no exercising, no delivery of any additional insulin bolus during the observation period).

Compliance with the study protocol will be evaluated by analyzing the information from the CRFs, insulin pump, and recorded CGM data. If participants do not follow the study protocol (i.e., receive an inappropriate dose of insulin, set an incorrect bolus, get an extra insulin dose or snack, or basal insulin suspension is not set appropriately), they will be considered non-compliant. Data from non-compliant participants will be used to perform an intention-to-treat analysis as a sensitivity analysis. If any CGM failure occurs during the study, only data from the glucometer will be analyzed. If the study regimen is interrupted by some factors, data concerning glucose values from the CGM and glucose meter will be collected until that moment.

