The calculation of insulin doses will be performed based on the individual’s ICR counted per 10 g of CHO. The normal bolus will be calculated as 6 × ICR, and the Super Bolus will be calculated as 150% × 6 × ICR, with the suspension of basal insulin for 2 h after the delivered prandial bolus. The CRF containing the protocol for both groups, the personal data, and the calculations concerning insulin doses will be filled in for both groups on the first day. A closed envelope with patient allocation will be attached to the CRF. In the next 2 days, patients will eat h-GI breakfast, and the bolus order will depend on the allocation group. Nurses who will not be involved in the study will administer the right type of bolus. To ensure that the study protocols will not be mixed up and remain blind, the nurse administering the premeal bolus will check the allocation in the envelope and will provide the appropriate type of bolus. The study duration per day is planned for 3 h. No additional meals, snacks, or correction boluses are allowed during this time. An observation time of 3 h is defined as an approximation of the total lasting hypoglycemic effect after a subcutaneous insulin bolus dose. The capillary blood glucose level will be measured with a Contour® Plus Link Meter at 0, 30, 60, 90, 120, 150, and 180 min after insulin administration with a continuously working monitoring system. There is a high possibility that rapid glycemic fluctuations will be observed after an h-GI meal. Therefore, the blood glucose level can be checked with both the CGM and glucometer to obtain the highest accuracy of glycemic level at the specified time point. Caregivers and patients will also be instructed to report symptoms of hypoglycemia with additional glycemia measurements. Hypoglycemia will be defined as the glucose level below or equal to 70 mg/dl (≤ 3.9 mmol/l), which is treated as a clinical hypoglycemia alert according to the ISPAD Guidelines 2018.^1^ If hypoglycemia occurs, the patient will receive 0.3 g/kg of glucose/saccharose. After 15 min, the glucose level must be controlled again. If hypoglycemia persists, the patient will receive the next dose of glucose/saccharose, until a glucose level over 70 mg/dl is achieved. The presence of hypoglycemia will not suspend the study process, and SMBG will be performed as it is established. The records from the CGM will be registered using the Medtronic Care Link Pro Software and discussed with the patients for educational purposes. The participants may discontinue the trial at any point in time without giving a reason. The researchers will make every effort to supervise, educate, and regularly control the patients to provide the proper study process.

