
### End points

The following is the primary endpoint:
Capillary blood glucose level 90 min after the administration of the prandial bolus as meals with h-GI typically cause blood glucose level peak within 60–90 min in T1D patients

The following are the secondary endpoints:
Capillary blood glucose levels at 30, 60, 120, 150, and 180 min after administration of the prandial bolusThe number of hypoglycemia episodes based on SMBG

The following data are based on the CGM:
Glycemic rise (GR)—the difference between the baseline and the maximum glucose valuePeak glucose level (PG)—the maximum value of glycemia during 3 h of post-mealtimeTime to PGArea under the blood glucose curve (AUC)Mean amplitude of glycemic excursion (MAGE)—the standard deviation of blood glucose (SDBG) obtained from all blood glucose concentrations within 3 h of post-meal timeTime in the postprandial glucose range between 70 and 180 mg/dl (4.0–10.0 mmol/l)

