Intention-to-treat analysis will be performed as a primary approach. Additionally, the data of participants who will finish the study according to the protocol (per-protocol) will be used as a sensitivity analysis.

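### The protocol article names intention-to-treat as both the sensitivity analysis and the primary analysis, so the population for the 90-minute glucose comparison is not fixed; a secondary rule stops glucose collection at an interruption

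*Protocol article*

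**What the plan says.** Two sections of the protocol article assign the analysis sets.

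- **Compliance:** a participant who departs from the protocol in a listed way (insulin dose or bolus error, unplanned insulin or food, basal suspension set wrongly) is classed as non-compliant. Then: "Data from non-compliant participants will be used to perform an intention-to-treat analysis as a sensitivity analysis".
- **Statistical analysis:** "Intention-to-treat analysis will be performed as a primary approach", and "the data of participants who will finish the study according to the protocol (per-protocol) will be used as a sensitivity analysis".

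Four further statements bear on whether the outcome exists for these children.

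- The primary endpoint (End points) is "Capillary blood glucose level 90 min after the administration of the prandial bolus".
- If the regimen is interrupted (Compliance), "data concerning glucose values from the CGM and glucose meter will be collected until that moment".
- After a low glucose value (Study procedure), "The presence of hypoglycemia will not suspend the study process, and SMBG will be performed as it is established".
- Data collection and management states: "Data concerning insulin requirements, HbA1c values, and anthropometric parameters will be gathered from non-compliant participants and those who cancel their consent".

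**The concern.** The primary population decides whose glucose values enter the main comparison. If one section makes intention-to-treat primary and another makes it the sensitivity analysis, either can be followed once the data are known, and each choice can be defended from the text.

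The choice is not neutral, because leaving out non-compliant children can bias the Super Bolus versus Normal Bolus contrast in two ways.

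- An extra insulin dose or a snack may be a response to high or low glucose, which is the outcome itself.
- Only the Super Bolus includes suspension of basal insulin. The suspension criterion therefore gives the Super Bolus day a way to fail that the Normal Bolus day does not have in the same form.

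Compliance is also judged partly from pump and CGM records, which carry information on treatment and on glucose. That is a further reason to fix the primary population in advance.

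The interruption rule is a smaller matter. An intention-to-treat analysis needs the 90-minute value even when the regimen was not completed, and the rule can stop collection before that value is taken.

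**Working it through.** **1. The two statements side by side**

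| Section | Intention-to-treat | Per-protocol |
|---|---|---|
| Compliance | sensitivity | not named; implied primary, since non-compliant data enter only the sensitivity analysis |
| Statistical analysis | primary | sensitivity |

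Both rows cannot hold. Neither sentence belongs to an amendment history, and no sentence says which section governs.

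**2. What the 20% in the Sample size section measures**

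Inputs from Sample size and Statistical analysis: difference 30 mg/dl, SD of paired differences 82, two-sided alpha 0.05, power 80%, withdrawal 20%.

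- n = ((1.960 + 0.842) × 82 / 30)² = 58.6, so 59 evaluable children.
- 59 / 0.80 = 73.75, so 74; 59 × 1.20 = 70.8, so 71; and 60 × 1.20 = 72.

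The stated 72 is reproduced to within 2. The 20% serves only to inflate the evaluable number for withdrawals. It is not a non-compliance rate, and the article gives none.

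**3. How exclusion moves the estimate**

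The Compliance section classifies participants, not days. In this crossover, excluding a child removes both test days. Let q be the fraction of children excluded, and let D_ret and D_exc be the mean within-child treatment differences in the retained and excluded children. Then

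D_all = (1 − q) × D_ret + q × D_exc, so D_ret − D_all = q × (D_ret − D_exc).

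Neither q nor the gap is in the documents. The values below are assumptions that show scale only.

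| q | gap 30 mg/dl | gap 60 mg/dl |
|---|---|---|
| 5% | 1.5 | 3 |
| 10% | 3 | 6 |
| 20% | 6 | 12 |

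Against the 30 mg/dl target these shifts run from 1.5 / 30 = 5% to 12 / 30 = 40%. If the gap is zero, there is no shift at any q.

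**4. What the interruption rule loses**

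Readings are due at 0, 30, 60, 90, 120, 150 and 180 minutes.

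- Interruption before 90 minutes: the 90-minute value is lost, and with it that day's primary endpoint, along with all later readings.
- Interruption after the 90-minute reading: only later readings are lost, and these serve secondary endpoints.
- Hypoglycemia alone: nothing is lost, because measurement continues.

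The Compliance section already has a research physician visit every 30 minutes up to 180 minutes, so the later readings are planned in any case.

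**The case against.** The best defence is that the Compliance sentence is loose drafting. The Statistical analysis section is the natural place to look, and it is explicit about both roles, so most readers would take intention-to-treat as primary. That is probably the intention, and it is why the correction is small. But the article does not say that one section overrides the other, so the contradiction stands.

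A reader might also infer several stronger points. The documents do not support them.

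- **That 14 of 72 children change status** (0.20 × 72 = 14.4). This treats the withdrawal allowance as a non-compliance rate. A child who withdraws without a 90-minute value contributes no observed outcome under either section.
- **That no glucose is collected from non-compliant children.** The list in Data collection and management does not name glucose, but it is not said to be exclusive. The Compliance sentence presupposes outcome data from these children, and the 30-minute schedule makes no exception for them.
- **That a wrongly set suspension is a reaction to glucose.** A nurse outside the trial programs the bolus, the pump screen is covered, and the suspension follows directly on the bolus. An error made then precedes the post-meal values. The suspension criterion matters because it belongs to one treatment only.
- **That any interruption costs the primary endpoint.** Only one before 90 minutes does. Interruption is also a different event from the listed forms of non-compliance.

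**Conclusion.** The point holds and should be corrected before analysis: the primary population is stated in two incompatible ways, and this decides who enters the 90-minute comparison. The conclusion rests on the text alone and needs no numerical assumption.

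The size of any resulting bias cannot be stated. It depends on how many children are non-compliant and on how far their within-child differences depart from those of the others, and the documents give neither. They also do not show that anyone intends to choose the population after the results; they only leave that open.

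The interruption rule is a real but secondary defect, limited for the primary endpoint to interruptions before 90 minutes.

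**What to change.** 1. Rewrite the Compliance sentence to agree with the Statistical analysis section. The primary analysis includes all randomised participants with available 90-minute glucose, by randomised sequence and period and regardless of compliance. Per-protocol is the sensitivity analysis.
2. Replace the rule that ends collection at an interruption. After an interruption or deviation, the scheduled glucose readings continue to 180 minutes unless consent to data collection is withdrawn. This concerns measurement only and alters no treatment rule.
3. Optionally, name the glucose outcomes in the list under Data collection and management. This is clarification only.

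The first change is one sentence. The second is a change of procedure, though it uses readings already scheduled, and it helps only children tested after it takes effect. Under the Monitoring section, changes are noted at the registry and notified to the bioethics committee, which is a small cost.
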